### Sociodemographic and medical variables

Sociodemographic and medical variables (T1) (e.g., smoking, alcohol use, age, parity, SES, ethnicity, gestational age, height and pre-pregnancy weight status, and work status) will be assessed with the pregnancy-adjusted Rotterdam Quality of Life interview [78] and using items derived from the DELIVER study [62].

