## Statistical methods

### Power calculation

The medium effect (Cohen’s d) of ACT treatment on depressive symptoms lies between 0.4 and 0.6 [30, 79]. With a significant α level of 0.05 and 80% power we have to include 290 women to detect a small to moderate effect size (Cohen’s d) of > 0.33 between intervention and control group. Based on previous ACT-trials with similar (or even smaller) sample sizes of non-pregnant moderately depressed individuals, a Cohen’s d of at least 0.57 was found with largest Cohen’s d for women with increased depression levels at baseline [45, 80]. Assuming an attrition rate of 18% as in previous trials evaluating the long-term effectiveness of ACT [45, 80], the current sample-size allows us to detect small to moderate effect sizes (i.e., d = 0.365) with a power of 80% at the planned follow-up assessment [81]. We aim to include approximately 60 midwifery practices that will approach about 6,000 pregnant women, for participation. Based on an estimated response of 62% [62], we will be able to enroll approximately 3500 women in the cohort study of whom ca. 15% will have depressive symptoms [82]. Of these potential trial participants, 20% and 25% are expected to refuse participation or will be excluded, respectively, arriving at about 290 pregnant women with depressive symptoms to be included in the RCT.

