### Statistical analyses

Analyses for the RCT will be done on both intention to treat (ITT) and per-protocol basis. First, to assess differences in depressive symptoms (EPDS) and resilience (i.e., well-being assessed with the MHC-SF) between intervention and control condition, independent t-tests will be used. The mean change of scores (T2-T1) will be standardized to interpret effect sizes in terms of Cohen’s d [83]. Next, ITT analyses will be performed using linear mixed modeling (LMM) to adequately deal with repeated measures data and clustering (i.e., at midwifery practice level). LMM’s with time, treatment, and time-by-treatment interactions will be performed to assess the intervention’s effectiveness in improving continuous primary outcomes of depressive symptomatology, resilience, and continuous secondary outcomes such as infant developmental milestones. Chi-square tests will be performed to assess group differences according to dichotomous (secondary) outcomes such as subclinical depression and flourishing incidence. Subsequently, generalized (binary) linear mixed models (GLMM) will be used to assess the intervention’s effect on the dichotomous secondary outcomes. To identify predictors of successful resilience training, (generalized) linear mixed models will be used. A multivariable GLMM to identify potential predictors of treatment success will be conducted in two steps: (1) univariable analyses to examine whether the potential predictor is significantly associated with the dichotomous outcome and (2) including significant predicting variables (*p* < .10) in the final multivariable model to identify independent predictors using the forward selection procedure. Finally, moderation and mediation analyses will be conducted to explore possible working mechanisms (psychological flexibility and mindfulness) of the intervention on maternal depressive symptomatology, resilience, and behavioral and infant developmental outcomes.

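### The two-step search for predictors of treatment success is prone to false and exaggerated predictors, and it finds prognostic factors, not modifiers of the treatment effect

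*Protocol article*

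**What the plan says.** The Statistical analyses section of the protocol article sets the aim: "To identify predictors of successful resilience training, (generalized) linear mixed models will be used". It then fixes a procedure: "A multivariable GLMM to identify potential predictors of treatment success will be conducted in two steps". Step 1 is "univariable analyses to examine whether the potential predictor is significantly associated with the dichotomous outcome". Step 2 is "including significant predicting variables (*p* < .10") "in the final multivariable model to identify independent predictors using the forward selection procedure".

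The section does not say which variables are candidates, which arm or arms enter this analysis, how success is dichotomised, or what p-value governs forward entry. It names no treatment-by-predictor interaction for this step.

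The next sentence plans something separate: "moderation and mediation analyses will be conducted to explore possible working mechanisms (psychological flexibility and mindfulness"). Under Sociodemographic and medical variables the article lists baseline items that could serve as candidates: "e.g., smoking, alcohol use, age, parity, SES, ethnicity, gestational age, height and pre-pregnancy weight status, and work status".

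**The concern.** There are two problems with the rule as stated.

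**It answers a different question.** A test of association with outcome finds women who do well. Success with the training, in the sense that the training helped, is a contrast between arms and needs a treatment-by-predictor term. Without one, a factor that predicts recovery equally under care as usual is reported as a predictor of treatment success.

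**The selection distorts what it reports.** Univariable screening followed by forward selection picks the largest chance associations and then estimates them on the same data. False predictors appear often, real ones are exaggerated, and the final p-values and intervals ignore the search.

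At stake is the credibility of this secondary analysis: general prognostic factors and chance findings may be reported as characteristics of women for whom the training works.

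**Working it through.** **1. Sample available.** The Power calculation section states: "With a significant α level of 0.05 and 80% power we have to include 290 women to detect a small to moderate effect size", with d > 0.33. Check: per arm 2 × (1.960 + 0.842)² / 0.33² = 144.1, rounded up to 145, so 290 in total. This reproduces. With the stated 18% attrition, 290 × 0.82 = 237.8, about 238 women or 119 per arm. The stated d = 0.365 at follow-up also reproduces (power 80.4%). The article gives no sample-size reasoning for the predictor analysis, so 119 (training arm only) and 238 (both arms) are used below.

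**2. Number of candidates (assumption).** About ten baseline items are named as examples. Nine measures stand under Mediators/moderators; satisfaction with the intervention is not a baseline variable, and hair cortisol is measured only in a subsample. That leaves seven, and 10 + 7 = 17. The article does not call these predictor candidates, so a range is shown.

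**3. Screen alone, no real predictors.** With k independent candidates, the expected number passing is 0.10k and P(at least one) = 1 − 0.90^k.

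| k | expected to pass | P(at least one) |
|---|---|---|
| 10 | 1.0 | 65% |
| 20 | 2.0 | 88% |
| 30 | 3.0 | 96% |

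**4. Full two-step rule, no real predictors.** Simulation with independent candidates and no clustering, 400 data sets per setting (Monte Carlo standard error about 2.5 percentage points or less). The 17-candidate runs used t-tests for the screen; the 20-candidate runs used logistic models with 50% success.

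| candidates | entry p | n = 119 | n = 238 |
|---|---|---|---|
| 17 | .05 | 60% | 58% |
| 20 | .05 | 65% | 64% |
| 20 | .10 | 88% | 87% |

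Each cell is the share of trials with at least one false independent predictor. As a check, 1 − 0.95^17 = 58% and 1 − 0.95^20 = 64%. A larger sample does not help, because the error comes from the number of tests.

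**5. Three real predictors among 20** (log-odds 0.3 or 0.5 per SD, both entry thresholds, both sample sizes). At least one noise variable was selected in 51–77% of trials. Noise made up 23–53% of all selected variables. Real effects of 0.30 that were selected averaged 0.52–0.56 at n = 119 and 0.39–0.41 at n = 238.

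**6. Prognosis against effect modification.** One predictor with log-odds 0.5 per SD and no interaction; 238 women, 2,000 data sets.

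| test at p < .10 | flagged |
|---|---|
| planned screen, both arms pooled | 97.6% |
| planned screen, training arm only | 83.0% |
| treatment-by-predictor interaction | 8.8% |

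A repeat run with a different seed gave 97.6%, 84.6% and 9.4%.

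**7. A case from the article.** The Power calculation section cites earlier ACT trials in which the effect was largest in women with more depression at baseline. That is an effect-modification hypothesis. Suppose the standardised baseline-to-T2 slope is r = 0.4 to 0.6 under usual care and the benefit grows by g = 0.1 to 0.2 SD per baseline SD (assumptions). In the training arm the slope is r − g, between 0.2 and 0.5, still positive. If success means a low EPDS score at T2, higher baseline EPDS then predicts failure in the training arm, although those women benefit more. The rule can point the wrong way.

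**The case against.** The strongest reply is that this is a condensed article. Arms, covariates and model terms may be settled in a fuller plan, and reading the absence of an interaction as its exclusion is an inference from silence. The wording is also modest (potential predictors), and a moderation analysis follows in the next sentence. Part of this stands: the candidate list, the arms and the entry threshold may well be set elsewhere, so the percentages are conditional on assumptions. But the article does fix the selection rule, and that rule is association with outcome. Adding an interaction would change the rule, not fill it in. The moderation analyses name only psychological flexibility and mindfulness as working mechanisms and leave the two-step output as it is.

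A reader might infer three stronger points that the document does not support:

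- *That the step finds mostly noise.* A simulation in which nothing is real makes every selection noise by construction. With three real predictors of 20, noise exceeded half of the selections in only one setting (n = 119, weak effects, entry at .10).
- *That the plan cannot tell who benefits from who recovers anyway.* This holds for the predictor step. The plan as a whole includes moderation analyses, whose coverage of other baseline factors is unclear.
- *That the results will decide who is offered the training.* The article does not state this use.

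It is also fair to say that the choice of a particular penalised method is partly preference, and that a trial sized for a main effect will detect few interactions.

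**Conclusion.** The point holds for this step. As stated, the rule identifies factors associated with outcome and labels them predictors of treatment success; a purely prognostic factor of moderate strength would be so labelled in about 83–98% of trials at the screen, against about 9% for an interaction test. When no candidate is real, the full rule yields at least one false predictor in about 58–65% of trials (17–20 candidates, entry p < .05) or 87–88% (20 candidates, entry p < .10), and weak real effects are overstated when selected. These figures assume independent candidates, no practice-level clustering and, in the 20-candidate runs, about 50% success. Fewer candidates would lower the false-predictor rates, but would not cure the confusion of prognosis with benefit. This is a secondary analysis; the primary comparison and the sample size are untouched.

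**What to change.** Reword the predictor analysis as follows.

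- Use both randomised arms.
- Pre-list a short set of baseline candidates, including baseline EPDS.
- Test treatment-by-predictor interactions within the planned mixed model, keeping practice-level clustering, and preferably on the continuous EPDS adjusted for baseline.
- Drop the univariable screen and forward selection. Fit one pre-specified model, with shrinkage or bootstrap internal validation; which of these is used matters less than fixing it in advance.
- Report the result as exploratory, alongside the planned moderation analyses. If a model of outcome association is still wanted, call its results prognostic factors.

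The cost is wording and a little more programming, with no extra data or participants. The real downside is that interaction estimates will be imprecise at about 238 women, so fewer predictors will be claimed.

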## Discussion

There is a lack of effective psychological interventions to reduce peripartum depressive symptoms and promote peripartum resilience. The present study is the first to examine the feasibility and effectiveness of a guided self-help ACT-based program for pregnant women with subclinical depression to decrease depressive symptoms and enhance mental resilience in the peripartum period. The RCT is embedded in a cohort study of pregnant women with follow-up assessments from early pregnancy up to 4 months postpartum. This cohort study explores the different trajectories of low to severe levels of depressive symptoms and examines the role of factors such as chronic stress, including maternal cortisol levels and resilience in relation to maternal mental health outcomes, birth- and infant developmental outcomes.

This study has several strengths: it will fill knowledge gaps concerning the effectiveness of interventions addressing the enhancement of resilience and the reduction of depressive symptoms among pregnant women with subclinical depression. If the ACT-based self-guided resilience training is shown to be effective, it will have important clinical implications as it is one of the first non-stigmatizing, easily accessible interventions for pregnant women. The ACT-based guided self-help intervention could fulfill an important role in the needed and strongly recommended prevention of peripartum clinical depression and its adverse consequences for both mother and child [85]. Using a self-help booklet with e-mail coaching may be particularly useful for women with mild to moderate depressive symptoms as it will probably result in better retention rates compared to face-to-face psychological or pharmacological interventions [20]. Furthermore, ACT has a unique transdiagnostic potential to affect a broader range of outcomes than depressive symptom reduction alone (e.g., anxiety and stress-related symptoms) and has shown to improve long-term outcomes even beyond the peripartum period [79].

Second, embedding this RCT in a prospective cohort study provides an excellent opportunity to examine trajectories of mental resilience factors and levels of peripartum depressive symptomatology in association with several maternal and child outcomes. To date, associations between resilience and psychological well-being have only been examined in non-pregnant populations, and associations between resilience factors and maternal or child outcomes have only been assessed in a few small-scale (longitudinal) studies [14–16].

Third, instead of cortisol from blood or saliva, antepartum hair cortisol levels will be assessed that are less invasive to obtain and will offer a more stable cumulative longitudinal measure of the maternal HPA-axis that can be linked to different levels of antepartum depressive symptoms and adverse maternal and child outcomes [86]. Furthermore, the association between antepartum resilience and chronic hair cortisol has only been studied once [87]. This study showed that pregnant women who were more resilient had lower hair-cortisol levels in the third trimester and less postpartum depressive symptoms, indicating the potential of resilience to prevent negative (mental) health outcomes in pregnant women and their offspring [87].

A limitation of this study is that multiple clinical self-assessments during the intervention period may reduce compliance and increase drop-out rates. However, we expect that continued participation will be encouraged through weekly positive interactions with the e-mail counselors. Compliance to fill out the baseline and follow-up assessments will be facilitated by using easily accessible online questionnaires. Another potential limitation is the maternal (and not paternal) report of infant developmental milestones, which might cause reporter bias, particularly in women with more depressive symptomatology.

In conclusion, the cohort data will deliver essential data to identify the role of resilience in relation to depression status during pregnancy and postpartum maternal and infant health. These longitudinal findings will also contribute to the development and strengthening of (existing) intervention strategies. With the embedded trial, the effectiveness of a pregnancy-adapted ACT-based self-help program in promoting resilience and reducing peripartum depressive symptoms will be evaluated. If successful, this will offer women and maternal healthcare providers a therapeutic option that is easy to incorporate into standard maternal care. Ultimately, it will also enhance more long-term resilience that may prevent postpartum mental health problems like depression, bonding difficulties, or postpartum traumatic stress.

## Data Availability

This is a study protocol; therefore, there are no data to share.

## Abbreviations

ACT: Acceptance and commitment therapy
CAU: Care as usual
HCC: Hair cortisol concentration
PPD: Postpartum depression
HPA-axis: Hypothalamic Pituitary Adrenal axis
CBT: Cognitive behavioral therapy (CBT)
